## Abstract

**Background:**

Human lactancy is a simple and cost-effective strategy that influences infant and maternal mortality rates. Skin-to-skin contact (SSC) is an immediate postpartum period strategy that has proven to benefit the initiation and continuation of human lactation and to decrease hospitalization during the first week of life. This study aims to determine the effect of SSC initiation at birth (immediate versus early) in healthy, full-term newborns treated at the Universidad de La Sabana Clinic on the duration of exclusive human lactation.

**Methods/design:**

A randomized, blind clinical trial will be performed with full-term healthy newborns born at the Universidad de La Sabana Clinic. The blind trial participants will be those persons measuring the results and analyzing the data. The sample size will be calculated for a type I error of 5 %, a two-tailed type II error of 20 %, and an estimated percentage loss of 30 %; 150 infants will be included in each group. Randomization will be performed using permuted, size-6 blocks. Descriptive analysis will be conducted using central tendency and dispersion measurements. A bivariate analysis will be performed to determine which variables are associated with exclusive lactancy at 6 months. For continuous variables, Student’s *t* test will be used for independent samples, and the Wilcoxon rank sum test will be used if the assumptions of normality for the *t* tests are not fulfilled. The assumption of normality will be evaluated using the Shapiro-Wilk and Kolmogorov-Smirnov tests. Categorical variables in contingency tables will be constructed to assess the independence between variables using the chi-square test, or Fisher’s exact test when the assumption of the number of cases is not met by the values in the contingency tables multiplied by two. This will be calculated as a measurement of the effect of relative risk (RR) with confidence intervals; the adjusted measurements will be calculated using a multivariate regression Poisson model. Variables with significant results will be used in the bivariate analysis, and those with biological plausibility will be used for the adjustment. The analysis will be carried out for a two-tailed type I error level of 5 %. The Stata 11 program will be used for data analysis. An interim analysis will be performed upon the submission of half the expected events (106), setting limits for the early termination of the trial according to the method proposed by Pampallona and Tsiatis (1994). Intervention: There will be two SSC randomization groups: early versus immediate. After completing the neonatal adaptation process and based on the group assignment, the mother will be left with her newborn child in hospital accommodation. Prior to discharge, the Infant Breast-Feeding Assessment Tool (IBFAT) will be applied. Monitoring will initially be performed with a face-to-face assessment between 3 and 10 days of life, followed by monthly telephone calls for 6 months to verify lactation status.

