##### Secondary outcomes

Human lactation capacity in the newborn within the first 24 h of life and prior to discharge using the IBFAT scale (Table 4)Maternal satisfaction with breastfeeding in the first 24 h according to the IBFAT scale (Table 4)Evolution of birth weight in the first week of lifeThe need for hospitalization in the neonatal care unit in the first week of life

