##### Instruments and times to assess the results

Newborn capacity for human lactation: the Infant Breastfeeding Assessment Tool – IBFAT (newborn human lactancy behavior) within the first 24 h of life and prior to discharge
Measurement of the change in weight from birth to the end of the first week of life: this will only be done with a previously calibrated electronic scale, which will take measurements at birth and in the first week of life. The need for admission to the NICU in the first week of life will be assessed during the first follow-up visit in the first the week of life (Additional file 1)Duration of exclusive human lactation: monthly telephone tracking of breastfeeding status will continue for 6 months or until human lactation is no longer the only food source (Additional file 2)

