#### Follow-up

▪ The first assessment will take place in the first week of life. The mother and the baby will be summoned to the Universidad de La Sabana Clinic and a nursing professional will perform it. This consultation aims to record the birth weight, the effectiveness of human lactation and feeding capacity and the need for hospitalization.▪ Monthly follow-up. This follow-up procedure will take place via monthly telephone calls with the mothers for 6 months, checking their adherence to human lactancy and, in the cases where breastfeeding has been suspended, inquiring about the reasons for this.

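### The abstract and main text disagree on when the first visit takes place, and neither puts it at or after the end of the week that two secondary outcomes cover

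*Protocol article*

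**What the plan says.** The abstract (Methods/design) gives the first visit a window: "Monitoring will initially be performed with a face-to-face assessment between 3 and 10 days of life". The Follow-up section places the same visit differently: "The first assessment will take place in the first week of life". It names no day within that week.

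Two secondary outcomes depend on this visit.

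- **Admission.** Secondary outcomes lists the "need for hospitalization in the neonatal care unit in the first week of life". Under Instruments and times to assess the results, need for NICU admission "will be assessed during the first follow-up visit in the first the week of life".
- **Weight.** The same section defines the outcome as "Measurement of the change in weight from birth to the end of the first week of life". The scale, however, is one "which will take measurements at birth and in the first week of life", so the second weighing is not tied to the end of that week.

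Follow-up describes the visit's purpose: "This consultation aims to record the birth weight, the effectiveness of human lactation and feeding capacity and the need for hospitalization". Later contacts are by telephone: "This follow-up procedure will take place via monthly telephone calls with the mothers for 6 months, checking their adherence to human lactancy". The article mentions no question about admission on those calls.

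**The concern.** The two descriptions of the visit cannot both hold: days 8 to 10 are allowed by the abstract and excluded by the main text.

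The conflict matters less than what the two texts share, which is that each allows a visit before the week is over. An outcome defined over a whole week is then read off at a point inside it. For admission, events after an early visit are never asked about, so the reported proportion is too low. For weight, infants are compared at different ages under one label.

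Admission in the first week is one of the two specific objectives, and weight evolution is a listed secondary outcome. The article says recruitment had not opened, so the timing could still be settled cheaply.

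**Working it through.** The plan gives no figure of its own to reproduce here. The check is arithmetic on the visit window.

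**Inputs**
- Abstract window: day 3 to day 10.
- Main-text window: within the first week, with no earliest day. Day 3 is kept as the earliest day (assumption).
- The first week is taken to end with day 7 (assumption; the article does not define it).
- A visit on day d captures admissions up to day d.

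**Unobserved days for admission** = max(0, 7 − d). **Age offset of the weight from day 7** = d − 7.

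| Visit day | 3 | 4 | 5 | 6 | 7 | 8 | 9 | 10 |
|---|---|---|---|---|---|---|---|---|
| Days unobserved | 4 | 3 | 2 | 1 | 0 | 0 | 0 | 0 |
| Weight offset (days) | −4 | −3 | −2 | −1 | 0 | +1 | +2 | +3 |

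**Average gap if visits are spread evenly** (assumption; the article gives no distribution)
- Days 3-10: (4+3+2+1)/8 = 10/8 = 1.25 days, or 1.25/7 = 18% of the week. Seen before day 7: 4/8 = 50%.
- Days 3-7: (4+3+2+1+0)/5 = 10/5 = 2.0 days, or 2.0/7 = 29% of the week. Seen before day 7: 4/5 = 80%.

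Preferring the main text therefore does not remove the admission gap. On this assumption it widens it.

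**Spread of age at weighing**
- Days 3-10: range 10 − 3 = 7 days; SD = √((8² − 1)/12) = √5.25 = 2.29 days.
- Days 3-7: range 7 − 3 = 4 days; SD = √((5² − 1)/12) = √2 = 1.41 days.

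**Illustration for weight.** Neither of the next two inputs is in the article: a gain of 20 to 40 g per day and a residual SD of 100 to 150 g. Share of variance due to age = (gain × SD of age)² / [(gain × SD of age)² + residual SD²].
- Days 3-7, low: 20² × 2 = 800; 800/(800 + 22,500) = 3%. High: 40² × 2 = 3,200; 3,200/(3,200 + 10,000) = 24%.
- Days 3-10, low: 20² × 5.25 = 2,100; 2,100/(2,100 + 22,500) = 9%. High: 40² × 5.25 = 8,400; 8,400/(8,400 + 10,000) = 46%.

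The share depends heavily on which window operates and on the outside inputs. It shows direction only.

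**The case against.** The strongest reply is that the sections defining the measurements confine the visit to the first week, and that one abstract sentence should not be taken as the operative window. That stands. A reader might infer that infants will be weighed up to 7 days apart, or that many will be seen after day 7. Both follow from the abstract alone; under the main text the spread is at most 4 days with day 3 as the earliest visit.

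A reader might also infer that a visit on day 10 would wrongly count later admissions. The documents do not support this. The outcome is limited to the first week wherever it is defined, and a visit on days 7 to 10 covers that whole week by recall.

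Nor is there support for reading this as bias between arms. The same timing applies to both groups, outcome assessors are to be blind, and nothing suggests that visit age would differ by arm.

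Finally, the visit form and call form (Additional files 1 and 2) and the schedule (Table 2) are not shown. They may record admission dates or ask about admission later. How age is handled in the weight analysis, and the varying names for the admission outcome, may likewise be settled there or in an analysis plan. Neither is relied on here.

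What survives is narrower: as the timing is stated, a visit before day 7 cannot see the rest of the week. A date recorded at that visit cannot recover an admission that has not yet happened.

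**Conclusion.** The point holds as a contradiction about visit timing, together with a measurement time badly matched to the outcomes. The abstract and main text need reconciling, and under either one an infant seen before day 7 has part of the admission period unobserved and no end-of-week weight.

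The gap is at most 4 of 7 days with day 3 as the earliest visit. The averages of 1.25 and 2.0 days rest on evenly spread visits. Observed time is not the same as events: the number of admissions missed also depends on when in the week they occur, which the article does not say.

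The consequence is an under-count of admissions and extra noise in weight change. The primary outcome comes from the monthly calls and is untouched. This is a worthwhile, inexpensive correction to two secondary outcomes, not a threat to the trial's main conclusion.

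**What to change.** 1. Reconcile the visit timing across the abstract, Instruments and times to assess the results, and Follow-up.
2. At the month-1 call already planned, ask every mother whether the infant was admitted and on what date, and count only admissions dated within the first 7 days. The article lets telephone tracking end once exclusive feeding stops, so this question should also reach mothers who have already stopped by then.
3. Record exact age at weighing and include it as a covariate in the comparison of weight change.

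The cost is one question on an existing call, one age or date field on the visit form and one model term, plus a call to any mother whose tracking would otherwise have ended. No extra visit is needed. The downside is about one month of maternal recall for admission. An infant seen before day 7 whose mother cannot be reached at month 1 would still be only partly observed and should be reported as such.

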**Discussion:**

SSC at birth has shown benefits in the short and long term for both the mother and the full-term newborn. Although the meta-analysis that have been done have shown the benefits of this technique, multiple differences in the SSC interventions have been identified because criteria such as the initiation or duration of SSC (dose) have not been unified. Colombia has a malnutrition risk of 11,4 % in the total population for the period 2012-2014, so it is necessary to promote strategies that generate a positive impact on the duration of human lactation, providing support from the clinical setting of humanized delivery which is included in the IAMI strategy (Instituciones Amigas de la Mujer y la Infancia – Friends of Women and Children Institution). Therefore, we propose that the initiation time of SSC in full-term new-borns is related to the duration of exclusive human lactation.

**Trial registration:**

Registered ClinicalTrials.gov Identifier: NCT 02687685. Registered on 2 February 2016. This study is not yet open for participant recruitment.

**Electronic supplementary material:**

The online version of this article (doi:10.1186/s13063-016-1587-7) contains supplementary material, which is available to authorized users.

## Background

### Scientific background and justification

The first 2 h of a baby’s life has been defined as the optimum time to begin human lactation. Skin-to-skin contact (SSC) between newborn and mother in this period improves the chance of successful lactancy in the first hour of life and in the long term [1, 2]. The exclusive use of breast milk is the optimal food for infants in the first 6 months. The SSC birth involves placing the naked newborn in the prone position on the bare chest of the mother, drying and covering the baby’s head with a cap and the baby and mother with a sheet. This strategy offers benefits to the mother and baby in both the short and long term. Secondary complications for the mother (e.g., mastitis) often lead to inadequate breastfeeding whereas adequate breastfeeding decreases rates of maternal postpartum bleeding and depression, leads to greater cardiorespiratory and thermal stability of the newborn and a decrease in the need for newborn hospitalization within the first week of life; it also initiates the colonization of the mother’s own gut flora in the newborn which leads to a decreased risk of infection [3–5], a lower incidence of infectious diseases in the first year of life, and a positive impact on reducing the risk of obesity and of contracting chronic noncommunicable diseases; these human lactation benefits are directly related to the duration of lactation [6, 7].

The SSC strategy has been applied at different times at birth and for different time durations, the latter being understood as being a dose of SSC. Depending on the time of initiation of the SSC intervention, it has been divided into subcategories (Table 1) [3]. Although the optimum duration for SSC has not been defined, it has been accepted that we must continue and maintain it at least until the baby has completed its first proper sucking of the breast and is physiologically stable [1, 3, 6]. In Colombia, in the 2013 Clinical Practice Guidelines of the Ministry of Health and Social Protection for healthy newborn care, it is recommended that SSC should be made immediately during the postpartum procedure while performing immediate interventions and postponing newborn adaptation measures in order to prevent the separation of the newborn from their mother in the immediate newborn period [8]. In the obstetric literature, it is not clear if the benefits of the strategy remain independent of the initiation time of SSC at birth [3]. In Colombia however, the average duration of exclusive lactancy is 1.8 months which is well below the worldwide recommendation; additionally, only 56.6 % of Colombian mothers feed their babies breast milk in the first hour of life [9]. Currently, widespread care practices for mothers and newborns in hospitals and care centers make it common for the mother and baby to be separated in the immediate moment following birth, breaking the bonding link between them at this time and altering the ratio and benefits deriving from this contact [10, 11].

**Table 1 Tab1:** Subcategories on the time of initiation of skin-to-skin contact (SSC) intervention

At birth or immediately	Very early	Early
When contact is made within the first minute of birth	Within the first 30 to 40 min after birth and after the mediate and immediate neonatal adaptation interventions have been carried out	At any time between the first hour and 24 h of life

Through conducting a randomized, blind clinical trial, this study aims to determine the effects of two different SSC initiation times (immediate versus early) on the duration of exclusive human lactation in healthy full-term newborns treated at the Universidad de La Sabana Clinic.

### State of the art

Variability is evident in both clinical practice and the obstetric literature for both the optimum start time for implementing SCC and its optimum duration, which has created heterogeneous strategy results in research studies as well as interpretation. No studies have been conducted comparing the different SSC initiation times regarding breastfeeding, while recommendations have been made to study whether the initiation time makes a difference in the benefits of the technique [3].

Interventions at birth and the practice of separating the baby from the mother at birth have negative effects on the initiation of breastfeeding. A cross-sectional study of the factors involved in the initiation of lactancy within the first hour of life was conducted in different hospitals in Rio de Janeiro between 1999 and 2001 [11], and found that human lactation occurring during the first hour of life was less frequent if infants were subjected to immediate interventions after birth (odds ratio (OR) 0.47, 95 % confidence interval (CI) 0.15 to 0.80), if mothers had no contact with their newborns in the delivery room (OR 0.62, 95 % CI 0.29 to 0.95), if mothers were undergoing caesarean section (OR 0.48, 95 % CI 0.24 to 0.72) and if mothers were treated at private institutions. Regarding practices that promote exclusive breastfeeding during the hospital stay postpartum, Bramson et al. [12] in California, USA, conducted a cohort study; the analysis of multivariate logistic regression showed that the following factors – intention of breastfeeding before birth, the sociodemographic characteristics of the mother and early SSC applied within the first 3 h of the birth – all correlated positively with exclusive human lactancy during the hospital stay. In addition, a link between the duration of the SSC (dose) and exclusive human lactancy was revealed and there is a directly proportional relationship between the dose or time and exclusive lactancy: contact time between 1 and 15 min (OR 1.37, 95 % CI 1189 to 1593), 16 and 30 min (OR 1.66, 95 % CI 1468 to 1888), 31 and 59 min (OR 2.35, 95 % CI 2061 to 2695), and more than an hour (OR 3.14, 95 % CI 2905 to 3405).

Carfoot et al. [13] conducted a randomized clinical trial in the UK in order to assess the effects of early SSC in healthy newborns over 36 weeks on the initiation and duration of human lactation. It included 204 mothers and their newborns who were divided randomly into two groups: early SSC (*n* = 102): initiated at birth, delaying the adaptation intervention until after contact, the duration was at least 45 min until the first feed was completed or the mother chose to withdraw the SSC and the control group, were receiving routine care (*n* = 102) understanding this to mean that once born, the routine adaptation interventions are applied, separating the newborn from the mother and/or parent. The investigators measured the success of the first breastfeed as a primary result and as secondary results they measured exclusive lactancy until 4 months, thermoregulation in the first hour of life and the mother’s degree of satisfaction. The IBFAT (Infant Breast feeding Assessment Tool) scale was used to evaluate the success of the baby’s first breastfeed. They found that the success of the first feed within the first hour of life was higher in the SSC group (mean 8 %, 95 % CI 1.6 % to 17.6 %) and also higher for the duration of exclusive breastfeeding until the first 4 months of life. Likewise, the thermal stability of the baby was better in the SSC group and mothers also reported greater satisfaction in this group.

Villalón et al. [14] in Chile, conducted a prospective randomized study with newborns of between 38 and 42 weeks’ gestation and weighing between 2500 and 4250 g at birth; the intervention group was defined as *early SSC* in which the baby and mother have contact at birth and SCC was continued for 4 h. The control group was defined as the *post-birth routine care* group in which the mother is separated from the newborn in order for adaptation care routines to be applied. They evaluated lactancy independent of whether suction took place at birth or not and they considered 2 to 4 h as adequate time for exclusive lactancy and inadequate for those requiring whole or mixed formula feeding. Significant differences were found in favor of the group using early SSC in exclusive breastfeeding at 24 h of life (89.9 % versus 63.3 %, *p* < 0.001), at discharge from hospital (93.3 % versus 66.7 %, *p* < 0.001), and at 14 days of age (78.8 % versus 56.2 %, *p* < 0.02).

The systematic review by the Cochrane Collaboration [3] found that the SSC has positive effects on human lactation during the first to fourth months of life (OR 1.82, 95 % CI 1.08 to 3.07) and a positive effect on the duration of lactancy (mean difference 42.55, 95 % CI −1.69 to −86.79). Trends in improvement in the overall scores of maternal affection during lactancy, as well as in maternal attachment behaviors, were also found. Other reported benefits are that the newborns cry less (mean difference −0.01, 95 % CI −8.98 to −7.04). No adverse effects were observed or reported. It is important to note that the reviewers reported limitations given the variability in the intervention (initiation time of contact and duration) and the definition of variables; proposing SSC initiation time subcategories (*immediate*, *birth*, *very early*, and *early*), thus highlighting the need for studies investigating the benefits of the technique in this field.

As to the time of SSC and its duration, Takahashi et al. [15] evaluated the effectiveness of the initiation time and the duration of the SSC using by three indices: the measurement of stress-related cortisol in saliva, circulatory evaluation of heart rate and respiratory adaptation, and oxygen saturation. They found that the body temperature at 60 min and 120 min was lower in the SSC *birth* group (*p* < 0.001) compared to the *very early group* (*p* < 0.05), but all remained within normal ranges. A faster heart rate stability was found in the SSC *birth* group compared to *early* (*p* = 0.001), there were no significant differences in respiratory adaptation. Stress levels as indicated by the cortisol level were lower in babies who were in SSC for more than 60 min compared to those who were in SSC for less than 60 min (*p* = 0.046). This study concludes that *early* SSC within the first 5 min of life, with a continuous duration of more than 60 min, reduces the stress on the baby and improves cardiopulmonary stability at birth.

In Iran, Aghdas et al. [16] evaluated the effect of immediate SSC efficacy for human lactation through a randomized clinical trial with first-time mothers, measured by the BSES (Breastfeeding Self-efficacy Scale) until day 28. The mothers were randomized into two groups: *early* SSC, in which the newborn was left in SSC with the mother from birth for 2 h, postponing interventions up until that point; and *routine care*, in which the baby was taken to the radiant heat lamp once the umbilical cord had been cut in order to proceed with the interventions. The success of the first breastfeed was evaluated as a secondary result using the IBFAT and the average first lactation. In the SSC group, the self-efficacy in human lactation (BSES) score was 53.42 (standard deviation (SD) 8.57) versus 49.85 (SD 5.5) in the control group (*p* = 0.0003). The successful initiation of human lactation was 56.6 % in the intervention group versus 35.6 % in the control group (*p* = 0.02) and finally, the initiation time of the first feed was 21.98 ± 9.1 min in the SSC group versus 66.55 ± 20.76 min in the routine care group (*p* = 0.001).

